### Analysis

We will conduct both descriptive and comparative analyses to evaluate the effectiveness of each dissemination strategy. Dissemination patterns within each arm will be summarized, including views, link interactions, and survey responses. Where possible, metrics will be standardized (eg, engagement per view or per dissemination unit) to compare across strategies that could have different scales of deliveries.

Differences between arms will be assessed using aggregated platform (YouTube)- and link-level (Bitly) metrics, as well as survey-based outcomes. For survey measures of trust in the video and vaccination intent, distributions will be compared across dissemination strategies using logistical regressions controlled for sociodemographic characteristics (age, gender, and race/ethnicity). Subgroup analyses (eg, by age group, including adults aged ≥65 y) will be conducted where feasible and will depend on the overall sample size and the distribution of participants within each subgroup.

We will examine indicators of dissemination efficiency, such as reach per dissemination unit (eg, per organization, per seed, or per advertising campaign) and engagement. These comparisons are intended to identify dissemination approaches with greater potential for scalability and sustainability in Indigenous communities. The study is not powered to detect predefined effect sizes. Instead, results will provide empirical benchmarks to guide dissemination strategy selection in larger implementation efforts.

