### Study Design and Dissemination Arms

In our trial, we will test 3 dissemination strategies for our intervention. The videos will be hosted on our university’s institutional YouTube channel, with separate versions in each focal language. Videos will be distributed through the following three dissemination approaches for one month:

Paid social media ads: videos will be shared through a paid ad campaign through Facebook and Instagram. They will be shared as posts with a link to the YouTube video. The audience will be targeted using geolocation through zip codes with high Indigenous populations in California (based on ICAB and census data), language including Spanish, and interests identified with our ICAB.Community based organizations (CBOs): ICAB-affiliated CBOs will share the links to the videos using their usual communication channels used with their members (eg, WhatsApp, social media, email lists, CBO websites).Individual seeds: We will recruit Indigenous-identifying participants from our previous survey (listed above) who consented to future contact. Each individual will receive a link and be asked to share the video with five or more contacts in their network using their preferred method (eg, SMS, WhatsApp, social media).

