### Data Collection

#### Outcome Measurement

Outcomes include dissemination performance and message impact across dissemination strategies. The primary outcomes were (1) dissemination reach, measured using platform-level analytics and link-level tracking, and (2) message trust and vaccination intent, assessed through a brief post-viewing survey. Secondary outcomes included engagement metrics (eg, views, watch time, and sharing behaviors) and self-reported changes in views or attitudes toward COVID-19 and influenza vaccination following exposure to the video.

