#### Data Collection

Data was collected through three complementary methods to capture both dissemination performance and message impact across strategies:

Survey: a clickable Qualtrics survey link was shared at the end of the video to collect post-intervention data. The brief survey assessed likelihood of flu and COVID-19 vaccination, reactions to the video, how the video was shared, and trust and engagement with the video. Participants who completed the survey were entered into a gift card raffle.Link dissemination tracking: Bitly was used to create individual and personalized links for each dissemination strategy (eg bit.ly/socialmedia). We made a single link for all social media ads, one link per organization for the participating CBOs; and one link per participant for the seeds. We used Bitly analytics to track link engagement, clicks, locations, referrals and type of devices used. All links will corresponded to the same YouTube videos.YouTube analytics: we used YouTube metrics to track platform-level spread and engagement including video reach metrics (impressions, click through rate, views, etc), engagement metrics (watch time, retention, likes, comments, shares), audience insights (age and gender, viewers) and follow-ups (end screen and cards).

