## Results

The study was funded in January 2023. Intervention development, including formative work and the co-creation and translation of vaccine promotion videos, was completed in July 2025. Dissemination activities and participant-facing data collection across all three study arms were conducted between October 6 and November 28, 2025, aligned with the COVID-19 and influenza vaccination season in the United States (Table 1).

Three dissemination strategies were implemented during this period. For the community-based organization arm, five community-based organizations participated in distributing the video links to their members using established communication channels. For the peer-to-peer dissemination arm, 68 Indigenous-identifying participants from prior research were recruited as individual “seeds” and provided with personalized links to share the videos within their social networks. In parallel, targeted paid social media campaigns were conducted on Facebook and Instagram using geolocation, language, and interest-based targeting strategies informed by formative research and guidance from the ICAB.

All dissemination activities concluded on November 28, 2025. Data from Bitly link tracking, YouTube analytics, and follow-up surveys were consolidated and prepared for analysis beginning in January 2026. Outcome analyses are underway, and primary results are expected to be submitted for publication in Spring 2026.

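### The logistic regression stated for trust and vaccination intent makes no allowance for clustering of respondents within five CBOs and 68 seeds, so the precision of the arm comparisons is likely overstated

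*Protocol article*

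**What the plan says.** The Outcome Measurement section lists among the primary outcomes "message trust and vaccination intent, assessed through a brief post-viewing survey". These are answers from individual respondents. The Analysis section gives the model for them: "distributions will be compared across dissemination strategies using logistical regressions controlled for sociodemographic characteristics (age, gender, and race/ethnicity"). It names no random effect, no generalized estimating equations (GEE) and no cluster-robust standard error.

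Delivery was by unit. The Results section reports that "five community-based organizations participated in distributing the video links to their members" and that "68 Indigenous-identifying participants from prior research were recruited as individual" seeds. Each seed was "asked to share the video with five or more contacts in their network". The Data Collection section describes a "single link for all social media ads, one link per organization for the participating CBOs; and one link per participant for the seeds". The Analysis section does use the delivery unit (organization, seed or campaign) for its reach and efficiency indicators, but not for the survey model.

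On how a response reaches the database, the Data Collection section says that "a clickable Qualtrics survey link was shared at the end of the video to collect post-intervention data". All the tracked links lead to the same videos.

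**The concern.** People reached through one CBO or one seed share a messenger and usually a community, a language and a social network. The Discussion treats the messenger as something that shapes trust, so the study's own reasoning predicts correlated answers within a unit. Adjusting for age, gender and race/ethnicity does not remove that correlation. A respondent-level logistic regression with ordinary standard errors counts every answer as independent, although the CBO arm holds only five independent units however many members reply.

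The Discussion hypothesizes that CBO and peer sharing will show more trust and message impact than ads. With five CBOs, one or two unusual organizations could produce that pattern by chance, and the uncorrected analysis would attach too small a p-value and too narrow an interval to it.

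**Working it through.** The article states no sample size, alpha, power or ICC, so there is no figure of its own to reproduce.

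**Inputs from the article:** 5 CBOs and 68 seeds (Results); one link for all ads (Data Collection); a logistic model with three sociodemographic covariates (Analysis).

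**Assumptions:** 10, 20 or 40 respondents per CBO, equal across CBOs; 1 to 5 per seed; 200 ad respondents treated as independent; ICC 0.01 to 0.05, taken to 0.10 for seeds; nominal two-sided alpha 0.05.

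**Formulas**, with m respondents per unit and n per arm:

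- Design effect: DE = 1 + (m − 1) × ICC. Effective n = n / DE.
- Variance ratio, CBO v ads: R = (DE/n_CBO + 1/n_ads) / (1/n_CBO + 1/n_ads).
- True type I error of the uncorrected test: 2 × (1 − Φ(1.96/√R)).

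**CBO arm against 200 ad respondents**

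| m per CBO (n in arm) | ICC | DE | Effective n | R | Type I error |
|---|---|---|---|---|---|
| 10 (50) | 0.01 | 1.09 | 46 | 1.07 | 5.8% |
| 10 (50) | 0.03 | 1.27 | 39 | 1.22 | 7.5% |
| 10 (50) | 0.05 | 1.45 | 34 | 1.36 | 9.3% |
| 20 (100) | 0.01 | 1.19 | 84 | 1.13 | 6.5% |
| 20 (100) | 0.03 | 1.57 | 64 | 1.38 | 9.5% |
| 20 (100) | 0.05 | 1.95 | 51 | 1.63 | 12.5% |
| 40 (200) | 0.01 | 1.39 | 144 | 1.20 | 7.3% |
| 40 (200) | 0.03 | 2.17 | 92 | 1.59 | 12.0% |
| 40 (200) | 0.05 | 2.95 | 68 | 1.98 | 16.3% |

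Worked line, m = 40 and ICC 0.05: DE = 1 + 39 × 0.05 = 2.95; R = (2.95/200 + 1/200)/(2/200) = 1.975; √R = 1.405; 1.96/1.405 = 1.395; two-sided tail 0.163.

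For the 40-per-CBO rows, a beta-binomial simulation (20,000 runs, true proportion 0.7) gave 7.4%, 12.2% and 16.4%.

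**Seed arm.** With one respondent per seed DE = 1.00. With two, 1.01 to 1.10 over ICC 0.01 to 0.10. With five, 1 + 4 × ICC = 1.04 to 1.40, so the true standard error is 1.02 to 1.18 times the uncorrected one.

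**Is the difference itself inflated?** This was checked by simulation for CBO v seeds with no true difference (200 v 204 respondents, ICC 0.05, true proportion 0.6, 20,000 runs). The mean log odds ratio was 0.009, close to zero. The mean uncorrected standard error was 0.204 against an actual standard deviation of 0.292, and the nominal 5% test rejected in 17.3% of runs. The loss is in precision, not in the average estimate.

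**The case against.** Four points can be made on the other side.

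- **Silence is not exclusion.** The article is condensed and no analysis plan is shown. A logistic regression can carry cluster-robust errors or a random intercept without contradicting the text, so a reader who infers that clustering has been ruled out goes too far. What stands is that the article states the model and its adjustment set for primary outcomes and, followed as written, that model gives standard errors that are too small.
- **The study has no power target and offers benchmarks.** True, and this softens the consequence. It does not remove it, because arms are still compared by regression and the Discussion states a directional hypothesis. The article calls the results benchmarks; it does not say that about confidence intervals, and it sets no alpha. The 5% test above is a yardstick only.
- **The size is assumed.** This stands. The Discussion expects drop-off, so small clusters are plausible, and at 10 per CBO with ICC 0.01 the error is about 6%.
- **The unit may not be traceable.** This also stands. A reader might infer from "one link per organization for the participating CBOs; and one link per participant for the seeds" that each survey answer can be assigned to its unit. Those links track clicks, and all lead to the same videos. The survey asks how the video was shared, but nothing says that it records which CBO or seed delivered it.

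**Conclusion.** The point holds, with limits. As stated, the model for trust and vaccination intent makes no allowance for clustering, so its standard errors are likely too small and its precision overstated. It would be tempting to conclude that the arm differences are overstated too; the simulation does not support that, since the estimates stay centered on the truth.

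The problem is almost wholly in the five-CBO arm. Under 10 to 40 respondents per CBO, ICC 0.01 to 0.05 and 200 ad respondents, the design effect is about 1.1 to 3.0 and the type I error about 6% to 16%. The direction follows from any positive ICC with more than one respondent per unit. The size rests on these assumptions and cannot be fixed from the article.

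**What to change.** First establish whether the survey data identify the delivering CBO or seed.

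**If they do:** fit the trust and intent models with that unit as the cluster, by a random intercept or by GEE with a small-sample variance correction, because five CBOs are too few for ordinary sandwich errors. Treat ad respondents as singletons, and state that campaign-level variation cannot be estimated from the single-link ad arm. Add a check that leaves out one CBO at a time.

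**If they do not:** report the arm comparisons of trust and intent as descriptive, with intervals inflated by a design effect over a stated ICC range (for example 0.01 to 0.05), and make no significance claims.

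**Cost:** where the unit was recorded, a sentence in the analysis section and a few lines of code. Where it was not, it cannot be added through the survey, because data collection closed on November 28, 2025, and the second route is what remains. Either way the intervals will be wider.

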### Ethical Considerations

This trial was registered at ClinicalTrials.gov (NCT07096245) and approved by the University of California, San Francisco Institutional Review Board (IRB #23‐38709). No personal or identifiable data were collected through YouTube, Bitly, Facebook, or Instagram analytics; these platforms were used solely to obtain aggregate dissemination and engagement metrics. All survey data were collected through a secure UCSF (University of California, San Francisco) Qualtrics account. Participants who completed the post-viewing survey provided electronic informed consent prior to participation and, if interested, were entered into a raffle for one of forty US $100 gift cards. Individuals recruited as peer-to-peer “seeds” were consented in advance and received $30 in compensation for distributing the intervention content within their networks.

## Results

The study was funded in January 2023. Intervention development, including formative work and the co-creation and translation of vaccine promotion videos, was completed in July 2025. Dissemination activities and participant-facing data collection across all three study arms were conducted between October 6 and November 28, 2025, aligned with the COVID-19 and influenza vaccination season in the United States (Table 1).

Three dissemination strategies were implemented during this period. For the community-based organization arm, five community-based organizations participated in distributing the video links to their members using established communication channels. For the peer-to-peer dissemination arm, 68 Indigenous-identifying participants from prior research were recruited as individual “seeds” and provided with personalized links to share the videos within their social networks. In parallel, targeted paid social media campaigns were conducted on Facebook and Instagram using geolocation, language, and interest-based targeting strategies informed by formative research and guidance from the ICAB.

All dissemination activities concluded on November 28, 2025. Data from Bitly link tracking, YouTube analytics, and follow-up surveys were consolidated and prepared for analysis beginning in January 2026. Outcome analyses are underway, and primary results are expected to be submitted for publication in Spring 2026.

## Discussion

This study was designed to compare how identical, community-informed vaccine promotion content performs when disseminated through different digital channels among Indigenous communities in California. We hypothesize that dissemination strategies that leverage trusted relationships, such as community-based organizations and peer-to-peer sharing, will demonstrate higher levels of trust and message impact compared to standard social media advertising, while paid ads may achieve greater overall reach.

As public health communication continues to shift into digital spaces, and as people rely on a growing number of virtual platforms to connect, it becomes more important to understand how health messages are shared and how the messenger impacts how people trust those messages. This project responds to a gap in health research by testing three different strategies to distribute the same vaccine information video to Indigenous communities in California, communities that have often been left out of traditional outreach. We compare broad social media ads, which are commonly used today, to more targeted approaches through trusted community organizations and through individual participants sharing within their own networks.

One of the strengths of this study is the combination of digital tracking tools, like Bitly and YouTube, with a post-intervention survey. This allows us to see how messages move across systems and gives us a way to compare which strategy leads to more views, engagement, and trust. These insights can help shape future campaigns by showing how public health information can be distributed in ways that are more meaningful and relevant for the people they aim to reach. In addition, we ensure accessibility of the message by making it available in four Indigenous languages spoken in California.

We do expect some limitations. For example, the success of the seed-sharing strategy depends on whether participants decide to share the video, and whether the people they share it with choose to watch it and respond to the survey. These steps are voluntary, and it is anticipated that there may be some participant drop-off.

This study will provide a practical and grounded model for testing how digital public health communication interventions are shared, especially when the goal is to reach communities who are not usually centered in public health campaigns, who may have less trust in government resources due to historical experiences, and who may be harder to reach or have other barriers (language, etc).
